### Usual care

The UC group will receive generic PFMX exercise instructions and demonstrations from the research coordinator at the initial post-operative time point (post-operative day #10-14) comparable to standard practice for RP patients at the study site. Participants will be instructed on how to contract the pelvic floor using verbal cues and biofeedback (self-observation of urinary control at the toilet). After the pelvic floor muscles have been identified, the UC prescription will consist of maximal voluntary contractions with escalating repetition volume every 2 weeks. Repetition volume will start at 30–60 repetitions per day during weeks 1–2; 60-120/day during weeks 3–4; and 120-150/day during weeks 5–6, and 150-180/day for weeks 7–26. Total daily contractions will be divided into multiple sets over the course of the day, aiming for 10–20 repetitions per set. The total number of repetitions will be divided equally between rhythmic (contract and relaxed over one second) and sustained contractions (contract and hold for up to 10s and relax). Table 1 provides a detailed description of the UC PFMX prescription and progression.

### Advanced Pelvic Floor Exercise (APFX)

Participants will start with the introduction of basic PFMX (comparable to UC) with a gradual integration of Pfilates and Hypopressive exercises until week 12. The Pfilates exercises will progressively integrate postures that engage and activate supportive abdominal muscles including the TrA, hip adductors, and gluteals. During each pose, participants will be asked to perform a series of pulses within a small range of motion while maximally contracting their pelvic floor simultaneously. Similarly, the Hypopressive techniques are gradually integrated in the prescription and progressed over 12 weeks. These exercises focus on diaphragmatic breathing and TrA activation in various static postures. Participants are instructed to perform three successive slow diaphragmatic inspirations, followed by a total expiration and apnea (breath hold). Each apnea will be performed for approximately 10–30 seconds while activating their TrA and intercostal muscles and rising of their hemidiaphragm [45]. APFX participants will be gradually progressed in postures and repetition volume, varying between PFMX, Pfilates, and Hypopressives. Weeks 13–26 comprise the maintenance stage where patients will maintain their prescription until the end of the trial. A detailed week-by-week description of the program is provided in Table 2 and Appendix A. Total APFX contraction volume reflects the volume prescribed in the UC group following post-operative weeks.

## Feasibility assessment

Prior pelvic floor training trials in PCa patients undergoing RP have observed recruitment rates of 21-70 % [21]. We will measure recruitment success through participant recruitment per week and record reasons for non-participation from those who inquire about the study and are eligible to participate but refuse. Adherence to the UC and APFX program will be measured through a logbook that is included in their respective manuals as well as a logbook completed by the research coordinator during the weekly telephone communication that will compare prescribed to completed volume of contractions. Retention will be assessed by measuring attrition throughout the intervention period and at each assessment. We will monitor and record non-severe and severe adverse events that occur to participants during the course of this study using the National Cancer Institute Common Terminology Criteria for Adverse Events version 4.0 [53].

## Outcome measures

Participants will complete five study assessments: baseline (approximately 1 week prior to RP), and at 2, 6, 12, 26-weeks post-operatively. Each assessment session will take place in Toronto, Ontario at the Princess Margaret Cancer Centre in the WE-Can Program. Participant demographics and self-reported disease and treatment-related variables will be collected at the baseline assessment.

### Urinary incontinence

UI will be assessed using the 24-hour pad test, a 3-day, bladder diary, and a single-item on the Patient-Oriented Prostate Utility Scale (PORPUS). The 24-hour pad test will be used to measure UI by assessing the quantity of urine lost in one day. A urinary leakage pad is measured after a 24-hour period and compared to the unused pad weight and is used to assess the severity of UI [54–56]. Patients will receive their pre-weighed pads (TENA® Men’s Protective Guards [57]) at baseline with accompanying plastic zipper storage bags which will be collected at their scheduled assessments. Additional pads per assessment will be provided in case of severe leakage. The pads will be individually weighed on an Ohaus® SP2001 (Ontario, Canada) scale, accurate to +/− 0.1 g. Continence is defined as a loss of ≤ 2 g of urine or the use of one or less pad per day [56, 58–60]. During the 24-hour period that the pad is worn, the participants will complete a frequency volume chart including urination frequency, times of UI, and if the pad was ever removed for a period of time. The 3-day bladder diary is a standard instrument for self-reporting voiding patterns. Items include fluid intake, frequency of toilet voids, episode of urine loss, nocturia, number of pads used, and activity during event for the three-day period. Bladder diaries are widely used in clinical trials assessing UI after prostatectomy [18, 29, 61–63]. Participants will be instructed to complete these 3 days prior to their scheduled assessment appointments. Finally, a single item regarding urinary leakage and bladder control is selected from the PORPUS as an additional self-reported measure of Post-RP UI that has been used in previous studies [64, 65].

### Pelvic floor muscle strength

Digital rectal examination of the pelvic floor by a specially trained pelvic floor physiotherapist is currently the standard clinical method for assessing pelvic floor strength and function [9, 17, 66]. Pelvic floor strength will be performed in the crook lying position and participants are instructed to lift and squeeze the pelvic floor muscles as strongly as possible for a maximum of 5 seconds. The best of 3 maximum contractions is recorded. The quality of contractions are graded using the 6-point Modified Oxford Scale (MOS) [67-69]: 0 = no discernible PFM contraction; 1 = flicker, or pulsing under the examining finger, a very weak contraction; 2 = a weak contraction, an increase in tension in the muscle without any discernible lift or squeeze; 3 = a moderate contraction characterized by a degree of lifting of the posterior pelvic wall and squeezing on the base of the finger with in-drawing of the perineum; 4 = a good PFM contraction producing elevation of the posterior pelvic wall against resistance and in-drawing of the perineum; 5 = a strong contraction of the PFM; strong resistance can be given against elevation of the posterior pelvic wall. This will be measured at baseline (approximately 1 week prior to surgery), and post-operatively at 6, 12, 26-weeks. The MOS has been used in multiple studies assessing pelvic floor muscle strength following RP [56, 59, 70, 71].

### Body composition

Research has shown that men who are overweight reported lower post-operative urinary function [72, 73]. Body mass index (kg/m^2^) will be calculated using participant’s height (m) and weight (kg). Body fat percentage will be assessed by bioelectrical impedance analysis (Tanita© 3000A, Tokyo, Japan). Waist to hip circumference ratio will be measured according to the World Health Organization protocol [74]. Waist circumference will be measured with the measuring tape positioned at the midpoint between lowest margin of the last palpable rib and the top of the iliac crest and hip circumference will be measured at the widest girth of the gluteal region.

### Quality of life

PCa-specific QOL will be measured using two widely used and psychometrically valid and reliable measures: the Functional Assessment of Cancer Treatment-Prostate (FACT-P) [75] and the PORPUS [75-78]. Additional urological symptoms are assessed using the valid and reliable, 7-item International Prostate Symptom Score (IPSS) [79, 80]. Erectile function is assessed using the 5-item International Index of Erectile Function (IIEF) scale, a widely used, psychometrically validated multidimensional self-report instrument evaluating male sexual function [81, 82].

### Physical activity

Recreational physical activity volume will be measured through the reliable and valid 3-item Godin Leisure-Time Exercise Questionnaire – Leisure Score Index (GLTEQ-LSI) [83, 84] . The GLTEQ-LSI assesses the frequency of mild, moderate, and strenuous bouts of leisure physical activity or exercise performed for at least 15 minutes over the past week and has been previously used in trials with PCa survivors [65, 85].

## Statistical analysis

Participant characteristics at baseline will be compared using independent sample t-tests or chi-square tests. We will report retention and compliance rates for the sample and their associated 95 % CI as well as reasons for non-participation of eligible patients. To calculate outcome capture, we will calculate the proportion of participants who have complete data on each outcome at each time point divided by the total number of study participants. Estimates of efficacy (Group and Time main effect, as well as Group x Time interactions) will be analyzed using a repeated-measure analysis of covariance (ANCOVA), controlling for the baseline value of the outcome of interest. We will examine the effect size (Cohen’s d) of the intervention on the clinical outcomes by dividing the observed mean between-group difference in change in the outcome measure from baseline to follow-up (UC vs. APFX) by its standard deviation.

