### Study population/participants

Eighty-eight participants will be recruited for this trial. We anticipate an attrition rate of 20 % by the 26-week follow-up assessment to yield 70 participants (35 participants per group) for main efficacy estimate analyses that is aligned with recommended pilot and feasibility study sample sizes for treatment effect estimates [47–49]. *Inclusion Criteria*: Patients that: i) have localized PCa who have consented for RP (open retropubic, laparoscopic, or robot-assisted laparoscopic); ii) are between the ages of 40 and 80 years; and iii) are proficient in English. *Exclusion Criteria*: Patients that: i) are diagnosed with a known neurological disease, autoimmune connective tissue disorder; ii) have prior experience with pelvic floor training by a healthcare provider; iii) have uncontrolled hypertension; iv) have diagnosed chronic obstructive pulmonary disease (COPD) and/or chronic restrictive respiratory disease; v) have a history of inguinal herniation; or vi) have hypertonic pelvic floor muscles upon baseline evaluation. Pelvic floor tonicity will be assessed by a specially trained pelvic floor physiotherapist via digital rectal examination. Hypertonic pelvic floor is determined by the physical examination findings of extrapelvic musculoskeletal and connective tissue examination, as well as the elements of patient history [50]. These patients who exhibit levator ani hypertonicity (tension myalgia) will be excluded as they can experience pelvic, urogenital, and rectal pain; tightness and spasticity; and adverse effects on sexual, urinary, and bowel function that may be exacerbated with contraction-based pelvic floor training [51, 52].

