### Study recruitment and randomization

Recruitment will occur in the Greater Toronto Area (total population 4.5 million) in urological oncology clinics and through presentations and/or information stands [52] set-up at local PCa support group meetings. These peer-support meetings often include men who have been recently diagnosed and are considering various treatments for PCa, including RP. Men who self-identify as eligible will receive further verbal and written information about the study. Those deemed eligible and are interested will be asked to provide written consent.

Participants will be 1:1 randomized to the UC and APFX groups, stratified by age (±60 years). Blinded allocation of the participants to their treatment groups will be performed via a process consisting of placing the intervention assignments into opaque envelopes, sealing and shuffling the envelopes, and sequentially numbering them with each new participant receiving an envelope in sequence of recruitment. The envelopes will be opened by the research coordinator with the participant following the baseline assessment, prior to RP Fig. 1.

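### Significance tests on baseline characteristics of randomised arms tell little about imbalances that matter, and BMI, linked by the protocol to urinary function, is not a covariate in the urinary models (minor)

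*Protocol article*

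**What the plan says.** In the Protocol article, the Statistical analysis section opens with the baseline comparison: "Participant characteristics at baseline will be compared using independent sample t-tests or chi-square tests". It gives no significance level, no threshold and no rule for acting on the results. The efficacy analysis in the same section is a "repeated-measure analysis of covariance (ANCOVA), controlling for the baseline value of the outcome of interest"; no other covariate is named.

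The Body composition section begins: "Research has shown that men who are overweight reported lower post-operative urinary function". It then provides for BMI, body fat percentage and waist-to-hip ratio to be measured.

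The section on recruitment and randomisation sets 1:1 allocation, stratified by age only, and says: "The envelopes will be opened by the research coordinator with the participant following the baseline assessment, prior to RP". On size, the section on study population says: "Eighty-eight participants will be recruited for this trial". Feasibility is the primary objective; efficacy on urinary incontinence is secondary.

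**The concern.** Two things do not fit together well.

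- **The tests answer a question that is already settled.** Random allocation makes the population difference between arms zero, so a significant baseline result is a chance result. A non-significant one says little about whether the imbalance present could affect the outcome. That depends on the size of the imbalance and on how strongly the variable predicts the outcome, not on the p-value.
- **The variable that the protocol links to the target symptom is not used.** The association with post-operative urinary function is the only reason given for measuring body composition. In the analysis as stated, BMI can appear only as one of the characteristics tested at baseline.

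At stake are the precision of the secondary urinary estimates and their exposure to a chance imbalance in BMI. These estimates matter somewhat because the pilot is meant to inform larger trials.

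**Working it through.** **Inputs from the Protocol article.** 88 men, 1:1, so 44 per arm. Baseline is assessed before the envelope is opened, so baseline data should exist for all 88. The recruitment target reproduces: 70 / (1 − 0.20) = 87.5, rounded up to 88.

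**Assumptions, not in the document.** Two-sided 0.05 for the baseline tests; BMI-outcome correlation r of 0.2 to 0.4.

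**1. Smallest observed imbalance that a t-test flags.** The standard error of a standardised mean difference is √(2/n) = √(2/44) = 0.213 SD. With 86 degrees of freedom the critical t is about 1.988, so the threshold is 1.988 × 0.213 = 0.42 SD.

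**2. What passes as non-significant.** With t = d × √(n/2) = d × √22:

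| Observed imbalance d | t | p |
|---|---|---|
| 0.2 SD | 0.94 | 0.35 |
| 0.3 SD | 1.41 | 0.16 |
| 0.4 SD | 1.88 | 0.064 |
| 0.5 SD | 2.35 | 0.021 |

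**3. Chance of a sizeable but unflagged imbalance.** Under randomisation, P(|d| ≥ 0.3 SD) is about 16%. Taking off the 5% that are significant leaves about 11% for any one continuous characteristic.

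**4. Typical imbalance.** The median absolute imbalance is 0.6745 × 0.213 = 0.14 SD.

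**5. Effect on the urinary estimate.** Shift in the group difference, in outcome SD = r × d:

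| | r = 0.2 | r = 0.4 |
|---|---|---|
| Typical, d = 0.14 | 0.03 | 0.06 |
| At the threshold, d = 0.42 | 0.08 | 0.17 |

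**6. Precision.** Adjusting for a covariate with correlation r removes a fraction r² of the residual variance: 0.2² = 4% to 0.4² = 16%. Here r should be read as the correlation that remains after the outcome's own baseline value is in the model.

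**7. Bias on average.** None. In simulated trials with no treatment effect and r of 0.2 or 0.3, the unadjusted comparison rejected in 4.7% to 5.2% of trials, in line with the nominal 5%.

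**The case against.** The case for leaving the plan alone is substantial.

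- **The text says only that characteristics are compared.** It does not say that p-values decide comparability or choose covariates, and the one named covariate is fixed in advance. A reader might infer that balance is to be judged by these tests, or that adjustment will be data-driven. The document supports neither. This stands.
- **A reader might also infer that the tests would often miss a 0.5-SD imbalance**, because the power of a t-test against a true 0.5-SD difference at 44 per arm is only 64%. That does not follow. Power refers to a population difference, which randomisation rules out. An imbalance actually observed at 0.5 SD gives p = 0.021 and is flagged every time. Nor should the baseline tests be assessed at 35 per arm: that is the number expected at week 26, and nothing restricts the baseline comparison to completers. The t-test threshold does not carry over to the chi-square tests.
- **The protocol does not promise to adjust for BMI.** It cites an association without an effect size, so there is no contradiction between sections. A fuller protocol or analysis plan, not shown, could add covariates, including age, the stratification factor. This also stands, and makes the BMI part an improvement to a stated model rather than the repair of an error.
- **The size is small.** Even the 0.17-SD shift is below one standard error of an unadjusted difference at 35 per arm, √(2/35) = 0.24 SD, and efficacy is secondary.

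None of this makes the planned tests informative, or gives a reason to leave out of the stated urinary model a variable that the protocol itself links to urinary function.

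**Conclusion.** The point holds as a minor one. The baseline tests address a null hypothesis that is true by design, and at 44 per arm they leave any observed imbalance under about 0.42 SD non-significant, prognostic or not. The stated urinary models omit BMI although the protocol links overweight to urinary function and collects the measurement.

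The consequence is some lost precision and exposure to chance imbalance, not bias on average. The shift is about 0.03 to 0.06 outcome SD for a typical imbalance and 0.08 to 0.17 SD for one at the threshold. These figures rest on the assumed 0.05 level and the assumed correlation of 0.2 to 0.4, which the document does not give. If the correlation is weaker, the gain shrinks in proportion. The primary feasibility outcomes are not affected.

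**What to change.** In the Statistical analysis section:

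1. Prespecify baseline BMI as a covariate, alongside the outcome's baseline value, in the repeated-measures ANCOVA for the urinary incontinence outcomes. Include it whatever balance is observed.
2. Replace the baseline t-tests and chi-square tests with descriptive summaries by arm: mean and SD, number and percentage, and standardised differences.

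The change is to wording only. It uses one degree of freedom per urinary model and needs no new data, visits or participants.

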## Discussion

PFMX continues to be the mainstay for conservative management of UI after RP; however, its efficacy is modest. One hypothesis for ineffective PFMX regimens is that the pelvic floor muscles are not adequately activated because ancillary pelvic and abdominal muscles are not concurrently engaged. Novel techniques to address UI secondary to pelvic floor muscle weakness and/or RP involve a more comprehensive strengthening of the pelvic floor and its surrounding structures. Studies have reported a higher maximal voluntary contraction of the pelvic floor when training the pelvic floor muscles and its surrounding muscles simultaneously (i.e. TrA, hip adductors, gluteal, diaphragm) [30–34]. These advanced pelvic floor training techniques include Pfilates and Hypopressives that also engage the TrA, rectus abdominis, gluteals, diaphragm, and hip abductors that enhance pelvic floor contraction. Synergistic training of abdominal and pelvic floor muscles presents a newer approach to the rehabilitation of pelvic floor dysfunction following RP.

The primary outcome of this pilot study is to determine the feasibility of conducting a full-scale RCT of a comprehensive pelvic floor conditioning program compared to conventional PFMX. Measures of outcome efficacy will also be measured in urinary function, pelvic floor muscle strength, and QoL. To our knowledge, this is the first study to examine the effect of a comprehensive PFMX regimen that includes Pfilates and Hypopressives for UI. The above-mentioned training techniques may prove to be an effective alternative in the conservative management of UI and the early recovery of continence after RP.

## Appendix A. Sample cueing instructions for Pfilates and Hypopressives exercises

### Pfilates exercises

Pfilates exercise incorporates a series of poses and plyometric exercises to compliment pelvic floor muscle training. This form of neuromuscular conditioning is a therapeutic alternative for basic pelvic floor muscle exercise that can be easily integrated into any regular exercise routine. In these exercises, the engagement of the external hip rotators, adductors of the thigh, transversus abdominis, and gluteal muscles will facilitate or induce pelvic floor activation.

For each Pfilates pose will follow a series of identical phases:

I. The positioning/movement: Here you will position yourself in the Pfilates pose and perform the movement a series of repetitions
II. The hold: during this phase you engage the active muscles and contract your pelvic floor muscles
III. The pulse (plyometric): In this last phase, you will perform a series of pulses, matching the number of repetitions in the first phase. (i.e. If you performed 10 repetitions in the movement phase, you will perform another 10 repetitions in the pulse phase).

### Hypopressive exercises

Hypopressives are performed mainly via the transversus abdominis activation. The goal of these exercises is to relax the diaphragm, which in turn decreases the intra-abdominal pressure and may activate the abdominal and pelvic floor muscles simultaneously.

Each pose will follow a series of identical phases:

I. Positioning of the pose
II. Three diaphragmatic breaths (rest breaths), described below
III. Apnea (breath hold) of 5-30 seconds
IV. Repeat these steps a total of three times for each pose

### Diaphragmatic breathing (rest breaths) – practice pose

1. Lie on your back on a flat surface with your knees bent and place your hands on the bottom of your ribs.
2. Breathe in slowly through your nose and open your upper chest as much as possible. You should feel your chest flare out ward with your hands.
3. Exhale fully through pursed lips.

### Apnea

To perform a correct apnea (breath hold) you must close your nose and mouth (glottal stop). When you are performing the apnea phase of the exercise, you will have fully **exhaled** from your last rest breath. At this point, with a glottal stop, perform an inhalation without taking air in. You should feel your stomach and abdomen lift and squeeze up to your ribcage. Each apnea is held for 10 to 30 seconds.

